### Rationale

Coronary artery surgery with and without cardiopulmonary bypass plays an important role in the treatment and management of ischemic heart disease. Both treatment strategies have their own advantages and disadvantages. On-pump strategies provide more complete revascularization and require fewer repeat interventions compared with off-pump surgery. However, the procedure is more invasive and is associated with cardiac as well as noncardiac surgery morbidity [8,9]. Major neurological complications after conventional cardiac surgery have been reported to occur in 3.1% of patients [10]. Additionally, neuropsychological dysfunction is increasingly being recognized as a complication of on-pump surgery. Cognitive deficits can be documented accurately [11] and may occur in up to 38% of patients [12]. The increasing awareness of the cerebral complications following on-pump surgery especially in the elderly [13] has led to a renewed interest in coronary surgery on the beating heart. The Utrecht Octopus method is a technique developed to avoid cardiopulmonary bypass and the complications associated with its use [14].

The role of off-pump surgery, however, is the subject of debate. Opponents emphasize the excellent results of conventional on-pump surgery and express their concerns about the safety, early anastomotic failure, and eventual incomplete revascularization related to off-pump strategies [15].

Moreover, although widely accepted, the suspected deleterious role of cardiopulmonary circulation in the genesis of adverse cerebral outcomes has not been completely proved, simply because an appropriate control group has never been available. A limited number of randomized clinical trials have directly compared coronary surgery with and without cardiopulmonary bypass circulation [16,17].

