**Figure 1 F1:**
[figure not shown]
**Algorithm MASS IIItrial.** Only patients eligible for off-pump can enter the study. *Crossing-over in presence of electric or hemodynamic instability.

**Table 1 T1:** Schedule of Measurements

	S	P	D	1 m	3 m	6 m	12 m	24 m	36 m	48 m	60 m
Angiograms	X		X								X
History/events	X	X	X	X	X	X	X	X	X	X	X
Anginal assessment	X	X	X	X	X	X	X	X	X	X	X
Medications	X	X	X	X	X	X	X	X	X	X	X
Physical examination	X	X	X	X	X	X	X	X	X	X	X
Electrocardiography	X	X	X	X	X	X	X	X	X	X	X
Echocardiography	X										X
Magnetic Resonance Imaging	X		X								
Neuropsychological tests	X		X		X	X					
Routine laboratory	X	X	X	X	X	X	X	X	X	X	X
ECG stress tests	X					X					X
Resource utilization	X	X	X	X		X	X	X	X	X	X
Quality of life	X					X	X	X	X	X	X
Cost-effectiveness		X	X								
Working status	X				X						

Abbreviations: S = preprocedural screening; P = procedure; D = discharge; 1 m = 1 month after intervention; 3 m to 60 m denotes months after intervention.

**Table 2 T2:** Definitions of Main Composite Primary End Points

**Cardiovascular death**	Cardiovascular mortality is included in the composite primary end point. Cardiovascular death includes fatal myocardial infarction, sudden death, untreated heart failure, fatal cerebral infarction, and hemorrhage and procedure-related fatal bleeding.

**Cerebrovascular accident**	Patients with a focal neurological deficit of central origin lasting more than 72 hours, or a focal neurological deficit of central origin lasting more than 24 hours with imaging evidence of cerebral infarction or intracerebral hemorrhage, or a nonfocal encephalopathy lasting more than 24 hours with imaging evidence of cerebral infarction or hemorrhage adequate to account for the clinical state. Retinal arterial ischemia or hemorrhage is also included. To fulfill the definitions of stroke, the deficit must be new, sudden in conset, and not attributable to any more likely alternative cause.

**Myocardial infarction**	Elevation of specific cardiac enzymes within 14 days of a revascularization procedure and presence of new Q waves in at least 2 or more contiguous leads and CK-MB elevation 5 × normal (see Appendix).

**Further revascularization**	The initial revascularization is considered completed when the patient is transferred from the operating room to bed. Refractory angina requiring revascularization was considered an end point.

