### Primary Composite End Points

The primary endpoint should be a composite of cardiovascular mortality, cerebrovascular accident, nonfatal myocardial infarction, and refractory angina requiring revascularization across 5 years of follow-up.

It is expected that the need for repeat revascularization after coronary surgery with or without cardiopulmonary bypass will be similar. As mentioned, a controversy discussed in the literature indicates that coronary surgery with or without cardiopulmonary bypass circulation has equal effectiveness in terms of myocardial revascularization. Therefore, repeat interventions can be a major clinical event. Therefore repeat interventions will be considered as early failure of treatment in this study. In addition, the use of cardiopulmonary bypass can be associated with considerable cerebral injury, in particular neuropsychological deficits [11,12]. So, the primary end point in the comparison of surgery with and without cardiopulmonary bypass is also a cerebral event. This is defined as the proportion of patients free of the combined event of fatal and nonfatal cardiovascular accidents and cognitive dysfunction, whichever occurs first, to be determined in-hospital and during the 5 years of follow-up.

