### Secondary End Points

The secondary end points in this trial include non-cardiac mortality, presence and severity of angina, quality of life using the SF-36 Questionnaire [18], and cost-effectiveness at discharge and at 5-year follow-up. In this scenario, we will analyze the cost of the initial procedure, hospital length of stay, resource utilization, repeat hospitalization, and repeat revascularization events during the follow-up. Exercise capacity will be assessed at 6-month, 12-month, and end follow-up.

In the MASS III trial, no difference is expected in cardiac outcome; nevertheless, cardiac death, myocardial infarction, and repeat revascularization procedures will be assessed in-hospital and at 1, 6, and 12 months and yearly thereafter. Cognitive function will also be assessed at baseline and at 1, 6, and 12 months. It is expected that most patients will show a decline in this early postoperative period. However, the rapid recovery and short hospital stay of the nonselected patients who undergo coronary surgery in our hospital without extracorporeal circulation suggest that the benefits of this strategy may be especially reflected in a reduction of neuropsychological injury in the early postoperative period.

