### Statistical Analysis Plan

Patients eligible for the MASS III trial are invited to the outpatient clinic to receive additional information. Candidates for the trial admitted to a referral hospital are visited by one of the trial monitors. After giving consent, patients are randomized. To ensure a reasonable balance, assignment is performed according to a computer-generated list of random permuted blocks that are unknown by the investigators. After randomization, patients are scheduled for the allotted treatment.

The goal of the main analysis is to compare the primary outcome events in this trial. Kaplan Meyer curves will be used for graphic comparison. All values are expressed as mean ± standard deviation or percentage. The continuous variables are compared by the Wilcox rank sum test, whereas the discrete variables are analyzed with Fisher's exact test. The occurrence of outcome events will be compared by means of Cox's proportional hazards model yielding a hazard ratio. The primary data analysis will be based on the intention-to-treat principle. Interim analyses will be carried out annually to evaluate the safety.

For both treatment strategies, the cost of diagnostic procedures, treatment procedures, complications, and short- and long-term differences in effects will be estimated. Marginal costs in monetary terms will be calculated by multiplying unit costs and marginal medical consumption as recorded for each patient.

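### Cox on the cerebral endpoint can give a modest false hazard ratio against off-pump, because cognitive dysfunction has no onset date and its first test may be at discharge

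*Protocol article*

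**What the plan says.** Under Primary Composite End Points, the article first gives a composite with no cognitive component, then adds a cerebral endpoint that it also calls primary. The wording is "This is defined as the proportion of patients free of the combined event", and the event covers "fatal and nonfatal cardiovascular accidents and cognitive dysfunction, whichever occurs first, to be determined in-hospital and during the 5 years of follow-up".

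The Statistical Analysis Plan section sets the comparison of primary outcome events as its goal, names Kaplan-Meier curves, and adds: "The occurrence of outcome events will be compared by means of Cox's proportional hazards model yielding a hazard ratio". It makes no exception for the cerebral endpoint. The same section names Fisher's exact test for discrete variables.

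The row "Neuropsychological tests" in Table 1 is marked at screening, discharge, 3 months and 6 months. The text under Secondary End Points instead lists cognitive assessment at baseline and at 1, 6 and 12 months, with no discharge test. That section also refers to "the rapid recovery and short hospital stay of the nonselected patients who undergo coronary surgery in our hospital without extracorporeal circulation". The only rate given for cognitive deficit is in the Rationale: it "may occur in up to 38% of patients". The Neurocognitive Evaluation section says that only a subset is tested and gives no size.

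**The concern.** Death, stroke, infarction and revascularization happen on a known day. Cognitive dysfunction is a state that becomes visible only when the battery is given, so any event time for it in a Cox model is a visit date. If the first visit is discharge, that date is itself affected by treatment. Off-pump patients who leave sooner would have their dysfunction recorded on earlier days. On those days the on-pump patients, equally impaired but not yet tested, would sit in the risk set as event-free. The model would read this as a higher off-pump hazard.

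At stake is a hazard ratio for an endpoint labelled primary. The error would run against the arm that the article expects to protect cognition, and would grow with the difference in stay. It is a separate matter from whether the arms are tested at comparable postoperative ages: it arises even if cognition is identical in both arms on every postoperative day.

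**Working it through.** **The plan's own figure.** The only sample size is 153 per group, based on 95% freedom from cardiac events and a decrease of at most 10%. Reading the 10% as relative (95% against 85.5%), two-sided 0.05, power 80%, no continuity correction:

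n = [1.960·√(2·0.9025·0.0975) + 0.842·√(0.95·0.05 + 0.855·0.145)]² / 0.095² ≈ 1.371 / 0.009025 ≈ 152.

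This is within a patient or so of 153 and contains no cognitive assumption. The article states no figure for the cerebral endpoint, so what follows uses assumptions, marked as such.

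**Upper bound.** Let the same share p be impaired in each arm, q = 1 − p, with every off-pump test before every on-pump test and no other events. For a hazard ratio θ (off-pump against on-pump), the Cox score equation for large samples is

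(1/θ)·ln[(θ + 1)/(θq + 1)] = θq·ln[(θq + 1)/(q(θ + 1))].

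Putting θ = 1/√q makes both sides equal √q·ln(1/√q), so HR = 1/√(1 − p):

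- p = 38%: 1/√0.62 = 1.27
- p = 30%: 1/√0.70 = 1.20
- p = 20%: 1/√0.80 = 1.12
- p = 10%: 1/√0.90 = 1.05

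**Overlapping test days.** Simulation assumptions: equal arms, 38% impaired at the discharge test, discharge day normal with SD 2, 3% new dysfunction at each of the 3- and 6-month tests, time from surgery, 153 per arm, Efron ties, two-sided 0.05. Ranges cover two sets of runs (1,000 and 600 per setting).

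| Off-pump discharge earlier by (assumed) | HR | False-positive rate |
|---|---|---|
| 0 days | 1.00 | 4% to 5% |
| 1 day | 1.05 to 1.06 | 7% |
| 2 days | 1.09 to 1.11 | 8% to 9% |
| 3 days | 1.16 | 13% to 14% |

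**What moves the result** (2 days earlier unless stated):

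- *Spread of test days*, with an added 10% late event rate and 153 per arm: mean day 9 against 7 gives HR 1.15 at SD 1.5 and 1.09 at SD 3. Rejections against off-pump are 12.7% and 7.7%, where 2.5% is nominal. Day 9 against 6 without overlap gives 1.24 and 25%.
- *Dysfunction rate*: HR 1.02 at 10% and 1.03 to 1.04 at 20%.
- *Time origin*: counted from randomization, HR is 1.05 with an assumed mean wait of 5 days, 1.02 to 1.03 with 10 days and 1.01 to 1.03 with 20 days.
- *Number tested*: 75 per arm at 38% gives the same HR, with a false-positive rate of 6% to 6.5%.
- *First test near day 30*, equal spread in both arms: HR 1.00, 4% rejections.
- *Nominal visit time for cognitive events*: HR 0.99 to 1.00, 4% to 6% rejections. The artefact disappears.

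**The case against.** The strongest reply is that the article fixes none of the conditions on which the bias depends. It words the cerebral endpoint as a proportion and names Fisher's test for discrete variables, so Cox is a possible reading and not the only one. The discharge test is in Table 1 but absent from the schedule under Secondary End Points. Whether events are dated at the actual day or the nominal visit, and whether time starts at surgery or randomization, are details that a condensed article may leave to the full plan. Intention-to-treat, with surgery scheduled after randomization, makes randomization a natural origin, and ordinary waits then nearly remove the effect. No length of stay is given, and the remark on short stay concerns nonselected off-pump patients, not the trial's arms.

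All of this stands as a limit on certainty and size. A reader might infer that the planned analysis will produce a false result against off-pump; the document does not support that. A reader might also take "It is expected that most patients will show a decline in this early postoperative period" as a dysfunction rate of 55% or 65%. At those assumed rates, 153 per arm and 2 days' difference, simulation gives HR 1.21 or 1.29 and false-positive rates of 24% or 45%. But a decline is not the yes-or-no dysfunction of the endpoint, no such rate is stated, and only a subset is tested.

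What the reply does not remove is that the article names Cox for outcome events, includes this one by its first-event wording, and has a table that places its first postoperative test at a treatment-dependent date. Under the other schedule the discharge artefact would go, but Cox would still treat visit dates as onset dates.

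**Conclusion.** The concern holds conditionally. If the first test is at discharge, events are dated at the actual test day, time runs from surgery, Cox is applied to this endpoint and off-pump patients leave earlier, then equal dysfunction can yield a hazard ratio above 1 against off-pump. At 38% dysfunction the size is small to moderate: about 1.05 to 1.16 for 1 to 3 days' difference with SD 2, with a ceiling of 1.27. If any one condition fails, the distortion shrinks to little or nothing. The false-positive rate matters mainly if all 153 per arm are tested. With about 75 per arm and 2 days' difference the test is close to its nominal level, although the estimate is still shifted.

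The days of stay, their spread, the wait for surgery and the late event rate are all assumptions. Only the cerebral endpoint in the tested subset is touched; the main composite and the sample size are not.

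**What to change.** 1. Keep Cox and Kaplan-Meier for events with a clinical date: death, stroke, infarction and revascularization.
2. Compare cognitive dysfunction as the proportion of those tested at each nominal visit, with a risk difference and 95% confidence interval. This fits the article's own wording of the endpoint as a proportion.
3. If the combined first-event endpoint is kept, use nominal visit intervals as the time scale, for example in a discrete-time complementary log-log model, so that the day of the test carries no weight.
4. Reconcile the cognitive test schedules of Table 1 (discharge, 3 and 6 months) and Secondary End Points (1, 6 and 12 months).

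The cost is wording in the analysis plan plus one reconciled schedule. The analysis change needs no additional patients, tests or visits, and no information on onset is lost because the test day carries none. One limit remains: a proportion at discharge is free of the dating artefact, but it still compares the arms at different postoperative days if cognition is changing quickly then.

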## Discussion

The MASS III Trial is designed to include patients who need coronary revascularization for relieving angina and better exercise tolerance. Off-pump surgery is a well-established alternative to on-pump surgery in terms of short and mid-term outcomes. However, the benefit of off-pump surgery may depend on the clinical status of patients and the majority of studies were carried out on low-risk surgical patients. Recently, patients with higher risk profile are increasing and in the context of elderly patients with comorbidities, the off-pump surgery might have an important role.

The lack of statement guidelines regarding this issue leaves the decision of using extracorporeal circulation to individual surgeons, and many of them remain unwilling to adopt off-pump surgery technique. This hesitation is still justified, since a more demanding technically procedure is being suggested instead of a successful, well-studied, and reproducible approach. Yet, if the benefits of off-pump surgery became conclusive, this would have several implications for the future of cardiac surgery regarding to quality of patient care as well as cost-effectiveness of the procedure. The MASS III trial is a great opportunity to address all these issues, and it will add relevant information in this field.

### Ethical Considerations

MASS III is conducted in accordance with the principles of the Declaration of Helsinki and with laws and regulations of our country. The Ethics Committee of the Heart Institute of University of Sao Paulo, Brazil approved the study protocol. The attending physician obtained written informed consent from the study participants. The patient is told that he or she will be randomized to surgery with or without extracorporeal circulation.

### Final Considerations

MASS III is designed to include patients who need coronary artery surgery and for whom 2 surgical strategies are feasible. The results of the study may facilitate selection of the most appropriate strategy for individual patients and foster the appropriate use of available resources.

## Appendix: Definition of myocardial infarction

**A** – Q-Wave infarction

See ECG-criteria new Q-wave infarction

Enzyme elevation as follows:

CK-MB elevation 5 × upper limit of normal

**B** – Enzymatic/non-Q-wave infarction

Enzyme elevation as follows:

CK-MB elevation 5 × upper limit of normal

**C** – ECG Criteria New Q-Wave myocardial infarction

New QS in 2 associated leads in the absence of left bundle-branch block (LBBB)/Wolf-Parkinson White Syndrome.

New QS in 2 associated leads, defined as ≥ 0.04 seconds broad and/or Q/R ratio ≥ 1/4

Posterior wall infarction: new Broad R-wave (≥ 0.04 seconds) and tall R/wave (R/S ratio▶1 or R-wave ≥ 0.5 mv) in lead V1 and V2 in the absence of right bundle-branch block (RBBB)/right ventricular hypertrophy (RVH)

New permanent LBBB and enzyme elevation

Reversed R-wave progression precordial: decrement R-wave ≥ 0.2 mv in 2 consecutive precordial leads and enzyme elevation.

Any new Q-wave in lead V2 and V3 and enzyme elevation.
